## 2 TRIAL DESIGN

BARACK D is a prospective randomised open blinded endpoint (PROBE) trial where neither the patients, GPs nor statisticians are blinded to the trial treatment. However, the primary endpoints will be assessed by an independent endpoint committee who are blinded to the treatment arm.

Eligible patients, from a minimum of 120 practices recruited by 6 NIHR School for Primary Care Research departments, with previously recorded blood test results suggesting CKD stage 3b will be invited to take part in the study and randomised between (i) ARA spironolactone 25mg OD on top of routine care and (ii) routine care.

Blood pressure in both groups will be titrated (monitored and adjusted accordingly) by the physicians against NICE guideline standards and routine checks of electrolytes undertaken. Primary outcome will be time to changes in cardiovascular events.

Appendix II displays the time schedule of trial procedures.

### 2.1 VISIT STRUCTURE

Potentially eligible patients will be invited by their practice to attend a baseline assessment and eligibility visit where the trial will be explained. Informed consent will be obtained and baseline assessments performed. Subsequent assessment will continue for both treatment arms for a further 36 months with follow up visits at weeks 1, 2, 4, 12, 26, and then every 13 weeks to 156 weeks. Windows either side of the visits will be two days for V1 and V2, 4 days at V3 and V4, 7 days for V5 and two weeks thereafter (all calculated from date of randomisation).

Patients will also be supplied with a validated home blood pressure monitoring machine along with an additional diary card, to record their self-assessed blood pressure for one week every 6 months. They will take two readings twice daily (e.g. 2 each morning and 2 each evening) over the week.

## 2.2 OUTCOMES MEASURES

The outcomes assessment schedule is shown in Appendix III.

### 2.2.1 PRIMARY OUTCOME

Time from randomisation until the first occurring of death or hospitalisation for heart disease (coronary heart disease, arrhythmia, atrial fibrillation, sudden death, resuscitated sudden death), stroke, transient ischaemic attack, peripheral arterial disease or heart failure or first onset of any condition listed above not present at baseline. Primary endpoints will be adjudicated by an independent endpoints committee blinded to treatment arm.

### 2.2.2 PRIMARY LONG-TERM OUTCOMES

Annual rates collected via medical notes review of death, hospitalisation for heart disease (coronary heart disease, arrhythmia, atrial fibrillation, sudden death, resuscitated sudden death), stroke, transient ischaemic attack, peripheral arterial disease or heart failure. First onset of any condition listed above not present at baseline.

The following variables will be used to record the occurrence of an event HOSPYN (hospitalised), FSONSETCVD (first onset of cardiovascular disease) and DEATHYN (death). In addition the endpoint will be adjudicated by the endpoint committee (DECISION). If the event is not judged to be an endpoint according to the protocol OR it is not the first onset of hospitalisation for CVD, or death OR there is insufficient information to determine it is an endpoint according to the protocol OR the endpoint committee determines it does not constitute as an endpoint for any other reason then the external adjudication will be coded "No". The reason that the event does not meet the endpoint condition will be captured in the variables REASONIFNO and OTHREASONIFNO. If any of the previously mentioned variables are coded "Yes" and DECISION is coded "Yes" then a primary outcome event will be recorded as having occurred.

If more than one primary outcome event has occurred, time to event will be computed using the date of the earliest occurring event minus RANDDAT (date of randomisation).

If a participant does not experience a primary outcome event they will be censored either at the date of last follow-up, the date of last contact or at the date of withdrawal from the study. Based on the intention to treat (ITT) principle, participants who withdraw from treatment but consent to further follow-up will be censored at the date of last contact rather than the date of withdrawal from treatment.

### 2.2.3 SECONDARY OUTCOMES

#### 2.2.3.1 TO DETERMINE THE EFFECT OF ARA IN PATIENTS ON MEASURES OF CARDIOVASCULAR HAEMODYNAMICS

##### Endpoints:

- (a) Change from baseline in office recorded systolic blood pressure annually (visit 7, 11) and at final visit. (variables SYSBPR and SYSBPL). Change in systolic BP is collected for right arm and left arm separately. Means of all measurements of BP (in particular measurements taken from different arms) will be calculated at each time point in accordance with NICE guidelines and these mean BP measurements will be used in the analysis. These variables are collected at each visit (see schedule of assessments in appendix III).

Rates of hypotension (<100mmHg systolic recorded in both arms or postural hypotension recorded) at any point during the study. The rates of hypotension across the study period, defined as <100mmHg systolic or >20mmHg systolic drop on standing. The outcome will be hypotension (a binary coded variable defined as hypotension at any point during the study period, coded 1, or no hypotension, coded 0).

- (b) This can be reported as two different outcomes:

- i. Hypotension (with or without symptoms) when systolic BP is <100mmHg. Specifically this variable is coded “yes” if systolic blood pressure in both arms drops below 100mmHg at any time point and “no” otherwise, i.e. {HYPO\_BP=yes IF (SYSBPR AND SYSBPL)<100mmHg} {HYPO\_BP=no IF (SYSBPR OR SYSBPL)≥100mmHg}. If this variable is coded yes at any follow up visit, then the outcome will be coded “yes”.
- ii. Postural / Orthostatic hypotension –postural or symptomatic hypotension leading to study discontinuation. If it is unclear whether the participant has symptoms it will be assumed that the participant has postural hypotension. This information regarding postural drop is recorded in the discontinuation CRF under EWDETAIL as free text and in the adverse event CRF. If postural hypotension is recorded at any time point this outcome will be coded “yes”

The variable HYPOTENSION will be derived as follows:

HYPOTENSION=1 if {(SYSBPR AND SYSBPL) < 100mmHg at ANY Visit} OR {EWDETAIL=”postural/symptomatic hypotension” at study discontinuation}

HYPOTENSION=0 if {(SYSBPR OR SYSBPL)>100mmHg at ALL Visits} AND {EWDETAIL postural/symptomatic hypotension”}

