### 9.5. Baseline Assessments

Potentially eligible patients will be invited to attend a baseline clinic at a trial practice where the trial will be explained. Informed consent will be obtained and baseline assessments performed.

A subset of patients will form the intensively phenotyped group who will undergo additional trial procedures as described below and in the procedure schedule (Appendix B). The intensive phenotyping of 24hr blood pressure and arterial stiffness in BARACK D will enable modelling of the extent to which any positive results may be explained by any blood pressure differences between study arms.

**Following consent**, all patients will have the following information taken and investigations performed at the initial baseline visit:

- Age
- Gender
- Self-assigned ethnicity
- Residential postcode
- Clinical history
- Past medical history
- Current medication
- Smoking status
- Physical examination
- Weight
- Height
- Waist circumference (using validated method)
- Office BP measurement using a British Hypertension Society validated automated device after 5 minutes rest
- Venepuncture for routine haematology and biochemistry including renal function (including eGFR calculated using MDRD and CKD-EPI formulae, hepatic and bone profiles, full blood count, fasting blood sugar, HbA1c, lipids, and, where local labs allow, BNP). Tests will be performed by a suitably qualified member of the Research Team (e.g. G.P. or research/practice nurse). Where appropriate to the Department of Health guidelines (e.g. routine tests) funding will be provided by the CLRN. Any outstanding costs will be met by the funder. Where transport and local coordination allows (initially involving specific practices within the Oxford recruitment area) an additional blood sample will be taken and stored for future genetic and protein testing.
- Urinalysis using albumin:creatinine ratio (ACR). Where transport and local coordination allows (initially involving specific practices within the Oxford recruitment area) an additional urine sample will be taken and stored for future testing.
- 12 lead electrocardiograph – where practice equipment availability allows
- Quality of life questionnaires (EQ-5D-5L and KDQOL-SF questionnaires, (ICECAP-A and QoL VAS – Oxford only))
- Issue diary card to monitor side effects of trial medication
- Pregnancy tests will be performed on women of childbearing potential, if deemed necessary, at the discretion of the physician

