## 9.6. Subsequent Visits

Subsequent assessment will continue for both treatment arms for a further 36 months with follow up visits at weeks 1, 2, 4, 12, 26, and then every 13 weeks to 156 weeks. Windows either side of the visits will be two days for V1 and V2, 4 days at V3 and V4, 7 days for V5 and two weeks thereafter (all calculated from date of randomisation). Measurements at each follow-up visit will vary according to the schedule in Appendix B but will consist of a combination of:

- Office BP measurement, using a validated automated device;
- Venepuncture for creatinine & electrolyte levels;
- eGFR (MDRD and CKD-EPI estimations);
- Monitoring for side effects.
- Additional bloods for fasting blood sugar and HbA1c, BNP (where local labs allow), lipids, full blood count and samples for future analysis;
- QoL questionnaires;
- Issue of drug monitoring diary card.
- Urinalysis using albumin: creatinine ratio.
- Home blood pressure measurement recorded on diary card.

Patients will also be supplied with a validated home blood pressure monitoring machine, along with an additional diary card and an instruction sheet, for 1 week every 6 months to document their self-assessed blood pressures. They will take 2 readings twice daily, i.e. 2 each morning and 2 each evening over the

week. The readings for the first two days will be discarded and the mean of the remaining readings taken as the home blood pressure level.

Physicians will be strongly encouraged to manage blood pressure according to NICE CKD guidelines (2008): Blood Pressure Targets: CKD and ACR <70 mg/mmol: systolic blood pressure target of <140 mmHg (target range 120–139 mmHg) and diastolic blood pressure target <90 mmHg. Choice of antihypertensive agents: ACE inhibitors/ARBs if not already prescribed will be offered to people with hypertension and ACR ≥30 mg/mmol. We estimate that around two thirds of patients in BARACK D will be additionally taking an ACE inhibitor or ARB. The remainder, (people with CKD and hypertension and ACR <30 mg/mmol) will be offered a choice of antihypertensive treatment according to the NICE guidance on hypertension (NICE clinical guideline CG127 or its update) to prevent or ameliorate progression of CKD.

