#### 4.2.2 THE EFFECT OF ARA IN PATIENTS ON MEASURES OF CARDIOVASCULAR HAEMODYNAMICS

Office measurements of systolic blood pressure (SYSBPR) at baseline, 6 months, 1 year, 2 years and 3 years will be summarised across treatment groups using means and standard deviations. Rates of hypotension (defined in section 2.2.2.1) across the whole study period will be summarised across treatment groups using numbers and proportions of those randomised to each arm. The rates of hypotension across the study period will be analysed by log-binomial regression models and predictors will be treatment allocation and GP practice. The treatment effect will be represented as a relative risk with 95% confidence interval and associated P-value.

The mean change in systolic blood pressure each year from baseline will be analysed with a linear mixed effects model. The model will include systolic blood pressure measurement at each time point and will adjust for baseline measurement and clustering within GP practice will be accounted for as a random effect within the model. An interaction between time and randomised group will be fitted to allow estimation of treatment effect at 6 months and 1, 2 and 3 years. Although 6 months and 1, 2 and 3 years are the main time points of interest, all visits at which BP is recorded will be included in the model to aid estimation of treatment effects in the presence of missing data. The model will also include a patient specific random intercept nested within a practice specific random intercept. Results will be presented as mean difference in change from baseline in systolic blood pressure between the randomised groups at 6 months and 1, 2 and 3 years, with 95% confidence interval and associated 2-sided p value.

The model will include the following fixed effects:

- Time
- Treatment allocation
- Time×treatment allocation
- Baseline systolic blood pressure

The model will include the following random effects:

- GP practice
- Participant ID

The distribution of the change from baseline will be formally assessed for evidence of departure from normality. If necessary, data will either be transformed or analysed using a non-parametric equivalent.

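### The SAP codes the postural part of hypotension by a narrower rule than its own definition and prose, and one relative risk then pools it with the measured part; align the code and report both parts beside the composite

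*Combined protocol and SAP*

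**What the plan says.** Protocol section 6 lists hypotension as a safety outcome with two limbs: a systolic pressure under 100 mmHg, or a systolic fall of more than 20 mmHg on standing. SAP 2.2.3.1 repeats this as "The rates of hypotension across the study period, defined as <100mmHg systolic or >20mmHg systolic drop on standing" and makes it one binary variable for the whole study.

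The SAP then says "This can be reported as two different outcomes". The first is HYPO_BP, which needs a systolic reading below 100 mmHg in both the right and the left arm at any follow-up visit. The second, item (b) ii, is postural or orthostatic hypotension. Its opening phrase restricts it to hypotension that led the participant to discontinue. Two sentences later it says "This information regarding postural drop is recorded in the discontinuation CRF under EWDETAIL as free text and in the adverse event CRF", and it closes with "If postural hypotension is recorded at any time point this outcome will be coded" as positive.

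Next comes the code, introduced by "The variable HYPOTENSION will be derived as follows". A participant scores 1 with a reading under 100 mmHg in both arms at any visit, or with postural or symptomatic hypotension entered in EWDETAIL at study discontinuation. The code has no 20 mmHg term and does not read the adverse event form.

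SAP 4.2.2 states the analysis: "The rates of hypotension across the study period will be analysed by log-binomial regression models and predictors will be treatment allocation and GP practice". It gives one relative risk, with no separate model for either limb.

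On measurement, protocol 9.5 describes the baseline reading as "Office BP measurement using a British Hypertension Society validated automated device after 5 minutes rest", and protocol 9.6 describes follow-up as "Office BP measurement, using a validated automated device".

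**The concern.** Hypotension is a named safety outcome for a drug that lowers blood pressure, and also a reason for stopping that drug under protocol 9.8. Its variable should therefore mean the same thing in the definition, the prose, the code and the analysis. Here the four do not agree, and they would classify some participants differently.

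The second issue is what the pooled variable measures. One limb comes from a scheduled reading in everyone. The other comes from text written when someone discontinues. Participants and physicians know the allocation (protocol 9.4 and 10.1.1), and the 9.8 rule stops trial medication, which only the spironolactone group takes. The chance that a postural episode is written down where the code looks for it may differ between groups even if the episodes do not. A single relative risk would not show the reader which limb produced it.

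**Working it through.** The plan states no expected rate, relative risk or power for hypotension, so there is no figure to reproduce. The check is a comparison of the texts.

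**Step 1. Can the 20 mmHg criterion be measured?** Protocol 9.5, 9.6 and Appendix B, and SAP Appendix II, list office and home blood pressure but no standing reading. Rest before the reading is specified at baseline only; the follow-up text is silent on posture. Standing pressure is therefore scheduled at 0 of the 15 follow-up visits (V1 to V15), in both groups. A fall on standing enters the data only if someone chooses to look for it.

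**Step 2. Where could a postural episode be recorded?** Item (b) ii names two sources; the code uses one of them. The adverse event form has its own limit. Under protocol 11.4 all adverse events are recorded for the first six months. After that the blood pressure item is a fall below 100 in both arms, and postural drop is not on the list. With V5 at week 26, that leaves 15 − 5 = 10 visits (V6 to V15) without it.

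**Step 3. What reaches the discontinuation form?** The 9.8 rule stops trial medication for a postural drop above 20 mmHg only when there are symptoms. A drop without symptoms meets the definition but triggers no stop.

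**Step 4. How do the rules classify the same person?** Take participants with no visit reading below 100 mmHg in both arms.

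| Participant | Stated definition | Item ii, opening phrase | Item ii, sources and closing rule | HYPOTENSION code |
|---|---|---|---|---|
| A: drop above 20 mmHg written on the adverse event form, not discontinued | Case | Not a case | Case | Not a case |
| B: discontinued for symptomatic hypotension, no drop above 20 mmHg documented | Not a case | Case | Unclear | Case |
| C: drop above 20 mmHg without symptoms, never measured | Meets it, but cannot be found | Not a case | Not a case | Not a case |

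A shows that the code undercounts against the prose. B shows that it also admits people whom the definition excludes. C shows why the stated definition cannot be delivered.

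**Step 5. What is modelled?** SAP 4.2.2 takes its definition from a section 2.2.2.1, a number the SAP does not contain. I read this as 2.2.3.1, and so as the HYPOTENSION variable.

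**The case against.** The strongest reply is that the code does follow part of the prose. The opening phrase of item ii ties the outcome to discontinuation, and the code implements that phrase. This is correct: the prose conflicts with itself and the code sides with one half. The conflict still needs resolving, because the named sources and the closing rule say otherwise.

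It can also be said that the two limbs already exist, that HYPO_BP has its own derivation, and that separate reporting is allowed. That stands, but the permission is not carried into SAP 4.2.2, which specifies one relative risk.

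Nor are adverse event records lost to the reader. SAP section 8 says hypotension is recorded in AETERM and summarised by group. Its cross-reference is to table 11, but the table with those rows is Table 7. A reader might infer that the Table 7 footnote should be changed to the coded definition. It should not: that table is built from adverse event terms, and the HYPOTENSION code would mislabel it.

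A reader might also infer that HYPO_BP should replace the composite or lead over it. The documents do not support that. The composite is the protocol's outcome. HYPO_BP is stricter than the protocol wording because it needs both arms. It depends on visits attended, and it can miss a treatment-limiting postural case if the drug is stopped before any reading falls below 100 mmHg.

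Finally, adverse event reporting is open-label too, so adding that form does not remove possible recording bias. That stands in full.

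**Conclusion.** The inconsistency is real and can be read directly from SAP 2.2.3.1. The code misclassifies participants against the SAP's own statement of sources and timing, and the 20 mmHg criterion in the definition has no scheduled measurement behind it. The pooled relative risk may therefore partly reflect unequal recording.

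A reader might go further and conclude that the relative risk is biased against spironolactone. The documents do not support this. Routine-care participants can also have entries on the discontinuation form, equal recording would cause no distortion, and nothing in the plan gives recording rates by group. Any numerical bias would rest wholly on assumed rates, so none is given. What can be counted is limited: no standing reading at 15 follow-up visits, one of two named sources used, and no postural item on the adverse event list at the last 10 visits.

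The point is minor. SAP 4.7 treats secondary outcomes as exploratory, and neither the primary outcome nor the mixed model for measured systolic pressure in SAP 4.2.2 is affected. It rests on two readings: that 4.2.2 models the HYPOTENSION variable, and that no standing reading was scheduled outside the procedures listed.

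**What to change.** 1. In SAP 2.2.3.1, add the adverse event form to the postural part of the HYPOTENSION code, and remove the restriction to events that led to discontinuation, so that code and prose agree.
2. Label that limb *clinically recorded postural or symptomatic hypotension (not systematically measured)*.
3. Make separate reporting a requirement. In SAP 4.2.2 give HYPO_BP its own log-binomial relative risk and show the postural limb by group, alongside the protocol composite and its relative risk. State beside the composite that its postural limb was not systematically measured.
4. Record the departure from the protocol's 20 mmHg definition in SAP section 11.

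The protocol 9.8 stopping rule and the Table 7 footnote stay as they are. The cost is SAP wording, one more source in the code and a little more analysis; no new data are needed. The change makes the variable consistent and lets a reader see which limb drives the result. It cannot supply standing pressures that were not scheduled, and because adverse event reporting is open-label it does not remove the possibility of unequal recording.

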|           | 5. Safety                                                                                      | 
 
Rates of hypotension (<100mmHg systolic or >20 mmHg systolic drop on standing)
 
Rates of adverse events
 
Rates of hyperkalaemia
 
                                                                           | 
 
Total occurrences
 
Total occurrences
 
                           |

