- 6.0-6.4 stop study drug and restart after 7 days on alternate days and if remains over 6.0 withdraw patient from trial treatment;
- >6.5 appropriate management and withdraw patient from trial treatment.

*Deterioration of renal disease:* If there is a deterioration of 20% in eGFR between visits or a deterioration of 25% from baseline to any visit, then withdraw the patient from trial treatment and refer to specialist care;

*Hypotension:* If there is >20 mmHg systolic postural drop in blood pressure with symptoms during the trial and/or the systolic blood pressure drops to below 100 mmHg then the trial medication will be discontinued;

If withdrawn from the trial, the reason for withdrawal will be recorded on the trial withdrawal form and if due to an adverse event, the Research Team will arrange for follow-up visits or telephone calls until the adverse event has resolved or stabilised.

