The safety analysis will focus on the adverse events. The safety population will include all participants who took at least one tablet of the study medication. Safety monitoring will invoke discontinuation rules for hyperkalaemia, deterioration of renal disease and hypotension. These will be recorded in the adverse event report form in the variable AETERM. These will be summarised by treatment arm as shown in table 11.

All adverse events (AEs) will be recorded at trial visits on the adverse event report form for the initial 6 months of follow-up by the member of the Research Team conducting that visit for the previous inter-visit period. Following this initial 6 month period, only the following AEs will be monitored by the member of the Research Team performing that visit in accordance with PC-CTU SOP TM19 "Pharmacovigilance": enlargement of breasts in men and women; erectile dysfunction; irregular periods; vaginal bleeding after the menopause; deepening of the voice in women, change in the tone of voice in men; excessive hair growth; tiredness; palpitations; and numbness and tingling.

All serious adverse events (SAEs) occurring during the study, either observed by the recruiting GP or reported by the participant, whether or not attributed to study medication, will be recorded on the CRF. The severity of adverse events will be assessed on the following scale: 1=mild; 2=moderate; 3=severe.

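### SAP 2.2.3.1 is inconsistent on whether postural hypotension recorded only on the adverse event form counts, and the coded variable leaves it out

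*Combined protocol and SAP*

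**What the plan says.** Protocol section 6 lists hypotension among the safety outcomes: systolic pressure under 100 mmHg, or more than 20 "mmHg systolic drop on standing". It attaches no condition about stopping treatment or leaving the study. SAP 1.4 repeats this.

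SAP 2.2.3.1 turns the outcome into a binary variable. Its opening text counts a low reading in both limbs or recorded postural hypotension at any point, and repeats the 20 mmHg definition. Item (ii), on the postural part, opens by tying the event to discontinuation. It then names two sources: "This information regarding postural drop is recorded in the discontinuation CRF under EWDETAIL as free text and in the adverse event CRF". It ends with the rule "If postural hypotension is recorded at any time point this outcome will be coded" yes. The formula that follows sets HYPOTENSION to 1 for a low reading in both limbs at any visit, or for postural or symptomatic hypotension in EWDETAIL "at study discontinuation". Neither line of the formula uses an adverse event variable.

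SAP 4.2.2 gives the analysis: "The rates of hypotension across the study period will be analysed by log-binomial regression models and predictors will be treatment allocation and GP practice". The result is a relative risk with confidence interval and P-value. SAP 8 says of the events behind the discontinuation rules, hypotension among them: "These will be recorded in the adverse event report form in the variable AETERM".

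**The concern.** The text and the formula of SAP 2.2.3.1 would lead two programmers to different variables. The programmer who follows the formula ignores a form that the SAP itself names as a source for postural drop.

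Cases recorded only on the adverse event form can arise. Protocol 9.8 stops trial medication for a drop of more than 20 mmHg only when it is a "systolic postural drop in blood pressure with symptoms during the trial". The outcome needs no symptoms, so a drop without symptoms may be written up as an adverse event and leave no discontinuation record.

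At stake is whether a protocol-defined safety outcome, compared between arms with a P-value, is measured as the protocol defines it.

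**Working it through.** The plan gives no figure to reproduce here, so the check is a comparison of texts.

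**Step 1. Which statements count an event recorded only on the adverse event form?**

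- Protocol section 6 and SAP 1.4: yes, since they set no condition on source or discontinuation.
- SAP 2.2.3.1, opening text and 20 mmHg definition: yes.
- SAP 2.2.3.1(ii), named sources and closing rule: yes.
- SAP 2.2.3.1(ii), opening words: no, unless the event led to discontinuation.
- SAP 2.2.3.1, formula: no.

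**Step 2. Apply the broader text and the formula to a participant whose systolic pressure is above 100 mmHg at every visit.**

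| Postural event recorded in | Broader text | Formula |
|---|---|---|
| EWDETAIL only | 1 | 1 |
| EWDETAIL and adverse event form | 1 | 1 |
| Adverse event form only | 1 | not 1 |
| Neither | 0 | 0 |

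Only the third row disagrees. If pressure is under 100 mmHg in both limbs at any visit, both give 1 whatever the postural record. In the zero line of the formula, the operator before the EWDETAIL text is absent from the text available. That may be a loss in conversion and is not counted as an error.

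**Step 3. Does another analysis supply the missing cases?** SAP Table 7 tabulates adverse-event hypotension by group under the same definition, so these events are reported. They do not enter the model in SAP 4.2.2. The populations also differ: SAP 4.2.1 and 4.3 put the secondary outcomes on the intention-to-treat population, while SAP 3.4 and 8 define the safety population by having taken medication. The column totals in the supplement show how far the two can part. Supplementary Table 1 (adverse events) uses 388 and 984, and Supplementary Table 2 uses 677 and 695. Both sum to 1372, and the spironolactone columns differ by 677 − 388 = 289.

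**Step 4. Size.** On the totals of Supplementary Table 2, each participant in the third row would change the proportion with hypotension by 1/677 = 0.15 percentage points on spironolactone or 1/695 = 0.14 on standard care. The documents do not give the number of such participants in either arm, so the effect on the relative risk cannot be calculated.

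**Step 5. How far can the adverse event form help?** Under protocol 11.4, all adverse events are recorded for the first 6 months, about 26 of 156 weeks (26/156 = 17%). Postural drop is not on the shorter list used afterwards. The visit schedule includes office blood pressure but no standing reading. Some postural events will therefore be on neither form, and no recoding can recover those.

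**The case against.** The strongest reply is that the formula does implement something the SAP says: item (ii) opens with the discontinuation condition. That stands, and it means the SAP conflicts with itself; the code does not contradict a settled definition. The narrow reading is still the weaker one. It leaves the mention of the adverse event form without a purpose, it clashes with the closing rule of the same item, and it departs from the protocol's outcome without being declared in SAP section 11, which lists only peripheral arterial disease.

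A second reply is that little may change. SAP 8 has the events behind the discontinuation rules recorded in AETERM, so the two forms may largely overlap, and nothing shows that cases on the adverse event form alone occurred. Table 7 reports that form's events in any case. This limits the harm but does not align the variable with its definition.

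A reader might go further and infer that the relative risk is biased against spironolactone, because the stopping rule acts on a drug that only that arm takes and the trial is open-label. The documents do not support a direction. The rule requires symptoms, and protocol 9.8 also says: "If withdrawn from the trial, the reason for withdrawal will be recorded on the trial withdrawal form". That applies to both arms. Adverse event reporting is open-label too, so adding it could itself bring in differential capture.

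**Conclusion.** The inconsistency is real. As coded, HYPOTENSION omits a participant with systolic pressure above 100 mmHg at all visits whose postural event is only on the adverse event form, although most of the SAP's own text and the protocol's outcome count that participant. This rests on taking the protocol's definition as the intended one.

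The size and direction of any effect on the relative risk are unknown. It would also be wrong to treat every postural event missing from EWDETAIL as lost through this formula: only those on the adverse event form are affected by it and recoverable. SAP 4.7 classes secondary outcomes as exploratory, and the primary analysis is not touched. This is a minor correction, worth making because it is nearly free.

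**What to change.** 1. In SAP 2.2.3.1(ii), delete the opening condition that the event led to discontinuation.
2. Set HYPOTENSION to 1 if systolic pressure is under 100 mmHg in both limbs at any follow-up visit, or if postural or symptomatic hypotension is recorded in EWDETAIL or in AETERM at any time. Set it to 0 otherwise.
3. Keep all randomised participants in the denominator, as SAP 4.2.2 specifies for the proportions. Participants with no follow-up reading and no record are then coded 0, and the SAP should say so.
4. Report HYPO_BP and postural hypotension separately by arm, which SAP 2.2.3.1(b) already allows. HYPO_BP rests on visit readings scheduled alike in both arms, so it is the component less open to differential capture.
5. State that postural capture is open-label and incomplete after month 6.

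The cost is a few lines of SAP text, a search of AETERM for postural and symptomatic hypotension, and the recoding of one derived variable. No new data are needed, and the protocol's outcome does not change.
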